**Fig. 3 Fig3:**
[figure not shown]
Study design and data collection components

To measure coverage of the intervention and changes in the CM domains and other key variables in each community over time, a cross-sectional, population-based survey was administered prior to the intervention and a second survey will take place following the intervention (Fig. 3). The surveys aim to capture 1200 randomly sampled adults, aged 18–49 years, from the HDSS population with approximately 75 people sampled in each of the 15 study villages at both time points. Eligibility criteria for participation in community surveys include residence in the home (spending a majority of nights at home), being 18–49 years of age, and having lived in the study area for at least 9 of the past 12 months. Surveys are interviewer-administered in the participant’s home using computer assisted personal interview (CAPI). Only one individual per household can be selected. Fieldworkers visit the selected homes to confirm eligibility and explain the study. Written informed consent is obtained from all participants prior to the survey; both consent and the survey are offered in the local language, Shangaan, or English. All procedures were approved by the Institutional Review Boards at the University of North Carolina-Chapel Hill and the University of California-San Francisco, the Human Research Ethics Committee (Medical) at the University of the Witwatersrand in South Africa, and the Mpumalanga Department of Health and Social Development Research Committee.

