### Study measures

#### Primary exposure

Residence in an intervention or control community is the primary predictor variable for all analyses. Community of residence will be determined using the HDSS data. Household and vital events data are updated annually and include births, in- and out-migrations and deaths. Although few individuals are expected to move within the study area over the course of the study, for those who do move, exposure will be determined dynamically over the course of the study such that individuals will be considered exposed if they were resident in an intervention community in the time period immediately prior to the outcome. Table 2 summarizes the quantitative data elements that include exposures, outcomes, mediators, and social and demographic co-variates.

**Table 2 Tab2:** Summary of quantitative data elements

Domain	Instrument/measure	Data source and frequency
Primary exposure		
Village	Village of residence (binary; intervention vs. control village)	HDSS-annual
Primary outcomes		
Testing uptake (aim 1)	Binary: tested/untested past 12 months, among HIV-negative or unknown status residents	Electronic health facility records-ongoing
	Binary: known HIV status–either confirmed positive or tested within the last 12 months	Electronic health facility records-ongoing
Linkage to HIV care (aim 2)	Binary: received baseline CD4 results and evidence of follow-up care (additional CD4, viral load, or treatment initiation) within 3 months of testing HIV positive	Electronic health facility records-ongoing
	Binary: treatment initiation within 3 months of positive diagnosis among those eligible for ART	Electronic health facility records-ongoing
Retention in HIV care (aim 3)	Binary: HIV patients on or initiating ART who have no more than a 90-day gap in medication received in the 12-month period (no defaulting).	Electronic health facility records-ongoing
	Binary: HIV patients not ART eligible^a^ who have a repeat CD4 test 6–12 months after initial CD4	Electronic health facility records-ongoing
Meditator/mechanism		
Community mobilization	Six domains of community mobilization measure [53]	Population-based surveys (years 1 and 5)
Covariates		
Demographics	Age, SES, gender, migration status	HDSS-annual
Social norms	Stigma [81]; gender norms [41]; community support for HIV testing and treatment [53]	Population-based surveys (years 1 and 5)
Secondary outcomes		

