For hypothesis 4, cross-sectional population data will be collected through representative community surveys. Summary measures of the CM domains before and after the intervention for each village will be calculated from this population representative sample. GEE will be used to model the effects of the pre-post differences in village-level CM domains on individual residents’ HIV testing, and, for HIV-positive individuals, linkage and retention to care using the same overall modeling approach as outlined above. To examine the relative importance of each of the six CM domains, initial models will include the pre-post change scores for each of the six domains in a single model. Subsequent analyses will isolate the marginal effects of each domain via G-computation or other substitution-based estimation strategy [60, 76].

Secondary analyses will extend GEE models to incorporate additional covariates of interest drawn from the HDSS data (e.g., age; gender) and examine their interactions with intervention assignment to ascertain statistical moderation. Secondary analyses will also evaluate whether the pre-intervention/post-intervention village-level difference in the six community mobilization measures mediate the relationships between intervention village residence and the primary outcomes. Statistical mediation will be assessed using the causal inference-based approach of Valeri and VanderWeele, which yields optimal estimates of indirect effects in the presence of binary outcomes and moderator-mediator interactions [77]. M*plus* will be used to implement these mediation analyses because it allows for causal mediation assessment incorporating robust standard errors to address clustering of individuals within villages [78]. Significant indirect and total effects of the intervention on testing, linkage, and retention accompanied by non-significant direct effects will signify mediation in this context.

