The Tsima ra rihanyu program is also rooted in community collaboration and feedback, with community participation in setting goals as well as monitoring progress towards reaching those goals. A key strength of this intervention is the ability to assess the care cascade in each community over time. In the first year of the intervention, we held goal-setting workshops with each intervention community to establish commitment and partnership towards improving HIV outcomes in the community. The concept of the UNAIDS 90-90-90 goals was introduced during these meetings and community leaders, and participants were able to both assess the current state of HIV testing and care outcomes in their community and establish annual community goals. Every 6 months, the team will hold a similar community meeting to monitor achievements towards reaching the goals and renew commitment and partnerships. Clinics are also receiving feedback on a regular basis, with a team discussion regarding where attrition is occurring in order for clinics to focus their efforts in improving clinical outcomes for their clients.

The study does have some limitations. The Tsima ra rihanyu program excludes use of mass media or large-scale public advocacy in order to minimize contamination in the context of an RCT. This omission will likely detract from the reach and impact of the intervention. Additionally, given substantial migration in the area, it is likely that some residents will be classified as lost to follow-up or out of care when they may have moved out of the area and remained in care. While information regarding changes in residency status (migration) and deaths are updated annually in the census and will be noted in the data, some residents captured in the electronic health facility data system may not present for return visits with no recorded reason for loss to follow-up. To remedy this, among those classified as lost, we will select a random sample of 10% to contact in order to determine their outcome, including whether they are seeking care elsewhere. This data will allow us to perform sensitivity analyses [80]. Additionally, we do not have current data on HIV status of all individuals in the community; therefore, the true number of residents living with HIV is unknown. We can, however, estimate the number based on previous population-based surveys in the area.

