## Conclusions

This will be one of the first studies to measure the impact of community mobilization on uptake of testing, linkage, and retention in care and to identify the mechanisms through which CM impacts engagement in care. Results can inform community-based initiatives in areas of high prevalence where uptake of TasP is most critical.

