## Trial status

The first cross-sectional survey was conducted between August-November, 2014. Data collection at health facilities in the study catchment area was rolled out across nine clinics between June and August 2015 and in an additional clinic from July 2016; clinic data capture is scheduled to continue in all clinics through 2018. Intervention activities commenced on 1st August 2015; the intervention is currently entering the second year of a 3-year intervention, scheduled to close out in July 2018.

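### Community mobilization is surveyed only before and after the intervention, so the plan cannot establish the mediator-before-outcome order that its mediation claim needs

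*Protocol article*

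**What the plan says.** Under Data collection, the CM domains are measured on two occasions: "a cross-sectional, population-based survey was administered prior to the intervention and a second survey will take place following the intervention". Table 2 lists the surveys for years 1 and 5 only. Trial status gives the calendar: "The first cross-sectional survey was conducted between August-November, 2014"; "Intervention activities commenced on 1st August 2015"; the intervention is "scheduled to close out in July 2018"; and clinic data capture continues through 2018.

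Under Analysis, each village's CM summaries from the two surveys are differenced. For hypothesis 4, "GEE will be used to model the effects of the pre-post differences in village-level CM domains on individual residents’ HIV testing", and on linkage and retention among HIV-positive residents, with the same general modelling approach as the primary analyses. Secondary analyses then treat the same village-level difference as a mediator between village assignment and the primary outcomes, using a named causal mediation method. The section also fixes a decision rule: mediation is declared when the indirect and total effects are significant and the direct effect is not.

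The Discussion describes goal-setting workshops in the intervention communities, at which current testing and care results were assessed. It adds: "Every 6 months, the team will hold a similar community meeting to monitor achievements towards reaching the goals and renew commitment and partnerships". The Conclusions say the study will be among the first "to identify the mechanisms through which CM impacts engagement in care".

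Aim 4 itself is milder. It sets out to explore CM changes and how domain differences relate to changes in outcomes.

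**The concern.** A mediation claim needs the mediator to come before the outcome. Here the mediator is a difference score that does not exist until the endline survey is done, while testing, linkage and retention are recorded throughout the preceding three years. A resident who tested in 2016 would have that test explained by a score completed in 2018 or later.

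The order matters because a return path is plausible in this design. Intervention communities review their own progress on testing and care every six months. Under Mediators: community mobilization, the shared-concern scale asks whether HIV testing and care are seen as important and open to change, and whether residents think they can act together. The collective-action scale captures how much activity takes place. Visible progress could lift both.

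If it did, villages with better outcomes would show larger CM change even if mobilization had no effect on care. The stated rule could then report a mechanism that the data cannot tell apart from the reverse.

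**Working it through.** The protocol gives no sample size, power or error rate for aim 4, so there is no figure to reproduce. The check is calendar arithmetic, followed by an illustration of what is at stake.

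**Inputs.** Launch on 1 August 2015, close-out in July 2018 and clinic capture through 2018 come from Trial status; capture is read as ending in December 2018. The 12-month testing and retention windows and the 3-month linkage window come from Table 2. The baseline survey took four months (August to November 2014). The endline survey dates are not given. It follows the intervention, so August 2018 is the earliest start. If year 1 is 2014, year 5 is 2018; that mapping is an inference.

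**Share of capture before the change score can be complete.**
- August 2015 to July 2018 = 36 months.
- August to December 2018 = 5 months.
- 36 / (36 + 5) = 36/41 = 88%.

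**Does any outcome window fit after the endline survey?**
- Testing and retention: 12 > 5, so none fits, whatever the survey date.
- Linkage: 5 − 3 = 2, so a 3-month window fits only if the survey ends within two months of close-out. If it takes four months, as at baseline, 5 − 4 = 1 month remains and 3 > 1, so none fits.

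**Would restricting to late outcomes restore the order?**
- A 12-month window ending July 2018 covers August 2017 to July 2018: 12 of 12 months precede close-out.
- A window ending December 2018 covers January to December 2018: 7 of 12 months precede close-out.
- So the order stays unresolved for the 12-month outcomes.

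**Could early clinic data serve as a baseline?** Nine clinics began capture between June and August 2015 and the tenth in July 2016, against a launch on 1 August 2015. The first captured year is almost wholly post-launch.

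**What a return path could do (illustration on assumed inputs, not trial estimates).** Take 8 and 7 villages, an intervention effect of 0.7 log-odds on the outcome, between-village SD s = 0.41, mediator noise SD t = 0.3, and no effect of CM on the outcome. Let the endline CM score respond to the outcome with slope r. The arm difference in CM is 0.7r, and the within-arm regression of outcome on CM has slope r·s² / (r²·s² + t²). The apparent share mediated is therefore r²·s² / (r²·s² + t²), with s² = 0.1681 and t² = 0.09.

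| r | Formula | Simulated share (4,000 runs) | CM–outcome path significant |
|---|---|---|---|
| 0 | 0% | about 0% | 5% |
| 0.25 | 0.0105/0.1005 = 10% | 11% | 21% |
| 0.5 | 0.0420/0.1320 = 32% | 31% | 59% |
| 1.0 | 0.1681/0.2581 = 65% | 65% | 96% |

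True mediation is zero in every row. The table shows that the planned analysis cannot distinguish the two directions. It does not show that a return path exists.

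**The case against.** Four replies have force.

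**Mobilization may have changed early.** The endline survey dates the measurement, not the change, and the score captures movement accumulated between 2014 and 2018. A reader might infer that the mediator itself comes after the outcomes, or that aim 4 can show nothing. The documents do not support that. What stands is that no planned measurement shows when CM changed, so the order is assumed.

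**The aim 4 outcome period is not spelled out.** A reader might infer that hypothesis 4 pools every outcome since August 2015. The Analysis section ties the time-averaged post-baseline comparison to hypotheses 1–3, and the shared modelling approach may mean only GEE, working correlation and robust errors. The analysis plan, not shown here, may fix the period. This does not rescue the mediation claim, because no 12-month window within the capture period can follow the endline survey.

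**The meetings belong to the intervention.** Goal setting with leaders is a listed activity in Table 1, so meetings that raise CM are the intended path. A reader might infer that reverse causation is built in, or that a spurious indirect effect will appear. That would require better results to raise CM more than poorer ones, which the protocol nowhere states. The possibility is real but not shown, and the simulated slopes are assumptions.

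**Much of the text is already cautious.** Aim 4 and hypothesis 4 use associational language, and mediation is a secondary analysis. This is correct, and it narrows the point to the effect wording and decision rule in Analysis and the promise in the Conclusions. Those statements are fixed in the article and go further than two surveys allow.

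**Conclusion.** The point holds as a limit on interpretation. With CM measured only before and after the intervention, 36 of 41 post-launch capture months precede the completed change score, and no 12-month testing or retention window can follow it. The plan cannot establish the temporal order its mediation analysis needs, and it cannot exclude that better outcomes raised the endline scores.

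This rests on the scheduled dates, on capture ending in December 2018, and on an endline survey held after close-out as stated. A later survey only strengthens it.

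The primary comparisons for aims 1–3, the randomized comparison of CM means between arms, and aim 4 as an exploration of association are all unaffected.

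**What to change.** In Analysis:
- For the CM change scores, replace the language of effects with associations.
- Delete the rule that declares mediation from a significance pattern.
- Report indirect-effect estimates with confidence intervals as exploratory, and state that the order of mediator and outcome is assumed, not observed.

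In the Conclusions, replace the promise to identify mechanisms with exploring associations consistent with the proposed mechanism.

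An analysis limited to the latest outcome windows may be added as a sensitivity analysis, with a note that it does not resolve the order. First-captured-year outcomes should not be adjusted for as if they were baseline. Capture began at about launch, so this would condition on outcomes the intervention may already have changed.

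The cost is wording and a weaker claim for aim 4, with no new data. An observed order would need a CM measure during the intervention, or longer clinic capture after the endline survey. Both require new data collection and are not part of this minimum change.

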#### Aim 4, mechanisms

To explore changes in community mobilization domains as well as how differences in each domain associate with changes in study outcomes (testing, linkage, and retention) over time.

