### Community randomization

Communities involved previously in community mobilizing activities (*n* = 12), those not yet fully enumerated in 2014 (*n* = 3), and with fewer than 500 permanent residents (*n* = 1) were not eligible to participate, leaving 15 communities to randomize. In order to achieve a balance among villages on the key covariates at baseline, a restricted or balanced randomization approach [54] was used, taking into account population size, distance to closest health facility, average levels of SES based on household assets [55], temporary migration, female-headed households, and baseline community mobilization scores [53], collected as part of a survey in 2014. Cluster allocation cannot be concealed as CM events and activities are held in public spaces. Further, village leaders were consulted about the trial, consented for their villages to participate, and were present for the allocation. A randomization event was carried out with community representatives. A biostatistician unfamiliar with the area and the villages generated 50 different grouped combinations of intervention and control villages, and these combinations were printed on strips. The assignment was revealed by asking a community volunteer to pick the winning randomization scheme out of a bucket containing all 50 possibilities. The program was then launched in the presence of local leaders and community members.

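### The aim 4 and mediation models use village change scores in community mobilization without the collected baseline score, which distorts the mobilization coefficient if attained mobilization, rather than change, drives care-seeking

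*Protocol article*

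**What the plan says.** All of this is in the Protocol article.

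- **Hypothesis 4 model (Analysis):** "GEE will be used to model the effects of the pre-post differences in village-level CM domains on individual" residents' HIV testing, and likewise linkage and retention for HIV-positive residents, with the modelling approach used for the primary outcomes.
- **Relative importance of domains (Analysis):** "initial models will include the pre-post change scores for each of the six domains in a single model".
- **Mediation (Analysis):** a secondary analysis will "evaluate whether the pre-intervention/post-intervention village-level difference in the six community mobilization measures mediate the relationships between intervention village residence and the primary outcomes". Mediation is declared when the indirect and total effects are significant and the direct effect is not.
- **Adjustment (Analysis):** the primary approach adjusts only for arm, time and their interaction. The extra covariates named for secondary models come from the HDSS, not from the survey that measures mobilization.
- **Baseline score (Community randomization):** the restricted randomization took account of "baseline community mobilization scores [53], collected as part of a survey in 2014".
- **Wording of the aim:** Aim 4 asks "how differences in each domain associate with changes in study outcomes (testing, linkage, and retention) over time". Hypothesis 4, in the Analysis section, is stated in terms of higher community means of the domains and their association with individual outcomes, that is, in terms of levels.
- **Timing (Trial status):** "Data collection at health facilities in the study catchment area was rolled out across nine clinics between June and August 2015", with a tenth clinic from July 2016. Activities began on 1 August 2015.

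**The concern.** Differencing a predictor removes stable village differences only if the outcome is differenced too. Here it can hardly be. Clinic capture started at most about two months before activities, so this source holds no 12-month pre-launch value of testing or retention. The model therefore relates an outcome observed after launch to a change in mobilization.

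A change score contains minus the baseline score. Villages that start high tend to show smaller gains, through regression to the mean and through sampling error in means of about 75 respondents. If a village's attained mobilization is what moves its residents, such a village may show good outcomes with little change, and the change-only slope is pulled away from the truth. Balancing baseline scores across arms does not cure this, because the slope is estimated across villages, including villages within the same arm.

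At stake is the reading of mechanism: a domain that matters could look weak, and true mediation could be missed.

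**Working it through.** The article gives no power, effect size or coefficient for aim 4 or mediation, so there is no stated figure to reproduce.

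**Inputs from the article:** 15 villages (8 and 7); six domains; about 75 respondents per village per survey round.

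**Assumed, because not given:** pre-post correlation of village scores rho from 0 to 0.9; post/pre SD ratio r from 0.7 to 1.5; arm effect on the post score d from 0 to 2 village SDs.

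**1. Slope if the attained level drives the outcome.** Let Y = b × post. With arm in the model, the change-only slope as a fraction of b is

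(r² − rho·r) / (1 + r² − 2·rho·r).

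- r = 1: (1 − rho) / (2(1 − rho)) = 0.50 at any rho below 1.
- r = 1.2, rho = 0.5: 0.84 / 1.24 = 0.68.
- r = 0.7, rho = 0.9: −0.14 / 0.23 = −0.61.
- r = 1.5, rho = 0.9: 0.90 / 0.55 = 1.64.

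With arm left out and r = 1, the between-arm shift adds k = (8 × 7 / 15²)·d² = 0.249·d² to both terms, giving (1 − rho + k) / (2(1 − rho) + k). At rho = 0.5 this is 0.50 for d = 0, 0.60 for d = 1 and 0.75 for d = 2. Over the whole assumed range it runs from 0.50 to 0.92. Adding the baseline score returns 1.00 in every case, measurement error aside.

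**2. Slope if change drives the outcome.** With Y = b × (post − pre), the change-only slope is b. There is no bias.

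**3. Mediation, attained-level case, r = 1, arm in the model.** Let the arm raise the post score by δ. The total effect is b·δ. The change-only slope is b/2, so the indirect effect is b·δ/2 and the direct effect is b·δ − b·δ/2 = b·δ/2, although the true direct effect is zero. Both shifts work against the plan's rule, which needs a significant indirect effect and a non-significant direct one.

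**4. Power by simulation.** Village-level linear regression, 15 villages, 4,000 runs, slope = residual SD = 1, arm shift 0.5 SD, arm in the model:

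| Model and driver | rho 0.3 | rho 0.5 | rho 0.7 |
|---|---|---|---|
| One domain, attained level: change only | 33% | 26% | 16% |
| One domain, attained level: change + baseline | 80% | 74% | 59% |
| One domain, change: change only | 93% | 86% | 70% |
| One domain, change: change + baseline | 81% | 75% | 60% |
| Six domains, attained level: change only | 20% | 15% | 11% |
| Six domains, attained level: change + baselines | 9% | 8% | 7% |
| Six domains, change: change only | 75% | 64% | 45% |
| Six domains, change: change + baselines | 9% | 9% | 7% |

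The joint model with baselines has 6 changes + 6 baselines + arm + intercept = 14 parameters on 15 villages, which leaves 1 degree of freedom.

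**5. Survey error.** With an assumed error of 0.5 SD and rho = 0.5, the one-domain slopes are 0.33 (change only) and 0.75 (with baseline) of the truth if attained level matters, and 0.67 with either model if change matters.

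**6. Arm comparison on a domain.** With equal variances, the variance ratio of the baseline-adjusted to the change-score comparison is (1 − rho²) / (2(1 − rho)) = (1 + rho)/2. At rho = 0.5 it is 0.75. Power of 80% on 13 degrees of freedom corresponds to a noncentrality of 3.03. Dividing by √0.75 gives 3.50, which on 12 degrees of freedom yields 89% (93% at rho 0.3; 85% at rho 0.7).

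**The case against.** The strongest reply is that the article names the effect of change as its target, in both the model description and aim 4. If change is the driver, the planned model is unbiased and adding baseline costs power. This stands. A reader might infer from the omission that the coefficient is biased outright, or always halved. The documents do not support that: they do not establish which mechanism holds, and exact halving also needs equal SDs and arm in the model. Nor does adjustment always gain power. In the joint six-domain model it loses power under either mechanism.

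Second, one-domain models cannot rank the domains and leave each coefficient open to confounding by the other five. This also stands, and is why the joint model should be kept.

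Third, the check is a linear village-level approximation, not the planned logistic GEE. That is a limit on the power figures. If village were entered as a fixed effect, one of the two options given, it would absorb a time-constant baseline score, but it would absorb the change score too. The hypothesis 4 slope as a main effect therefore needs the other option, alternating logistic regression.

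Fourth, outcomes could be studied as change across the roughly three years of capture. That is possible, and a true change-on-change model would not carry the halving. It would still lack a pre-launch 12-month outcome, and no such model is described.

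Fifth, covariates for mediation often sit in an analysis plan that is not shown here. The form of the mobilization predictor, however, is fixed in the article, each time as a change score.

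**Conclusion.** The concern holds in conditional form. The change-only models are right under one mechanism (change matters) and distorted under the other (attained level matters), and hypothesis 4 itself is worded in terms of attained means. In that second case the slope is 0.5 of the truth with equal SDs and arm in the model, 0.50 to 0.92 with arm omitted, and −0.61 to 1.64 over the unequal-SD range examined. The indirect effect is understated in the equal-SD case and a spurious direct effect appears.

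One domain at a time, the baseline-adjusted model contains the change-only model as a special case. At an assumed rho of 0.5 it risks about 11 points of power (86% to 75%) and stands to gain about 48 (26% to 74%). These figures rest on assumed effect sizes. For the arm comparison on domains, randomization leaves the change score unbiased, so the gain there is precision only.

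Nothing here touches the primary comparisons for aims 1–3. Aim 4 is exploratory and the mediation analysis is secondary.

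**What to change.** 1. For the arm comparison on each domain and for the exposure-to-mediator step, compare endline village means adjusted for the baseline village mean, in place of raw change scores.
2. In single-domain hypothesis 4 models and in the mediator-outcome models, include the village's baseline domain score alongside its change score, and report the change-only estimate next to it.
3. Keep the joint six-domain change model for relative importance. Do not add six baselines to it. State that its coefficients assume that change, not attained level, matters.

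The cost is wording in the analysis plan: the 2014 scores exist and the endline survey is already planned. The downside is one village-level degree of freedom per adjusted model, and lower power in the single-domain models if change alone is the driver.
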